#### 3.12.2 Secondary outcomes: clinical assessments

Improvement in depressive symptoms will be the main secondary outcome measure. Additional secondary outcome measures will include feasibility, safety, and tolerability metrics of rates of recruitment, withdrawals, and adherence, as well as the number and nature of AEs and serious AEs.

For continuous outcome measures, a mixed-effects model will be used to assess differences in the rate of improvement over time and the final outcome across groups. Treatment group, time, and treatment group × time interaction will be used as explanatory variables, with participant as a random factor. The significance of the treatment group × time interaction effect will be used to test the null hypothesis. For categorical outcome measures, response will be defined as a ≥50% reduction in HAM-D-17 and QIDS-SR-16 total scores at Visit 10. Remission will be defined as a HAM-D-17 total score of <8 at Visit 10. The two-tailed Chi-squared test will be used to assess the significance of any observed differences in the proportion of responders and remitters between groups.

#### 3.12.3 Secondary outcomes: electroencephalography

EEG data will be acquired at Visits 1, 5, and 10 to provide a time-series representation of changes in neural activity over time and after a single session of tTIS. These analyses will be exploratory. Two sets of recordings, before and after the tTIS or sham stimulation, will allow us to examine the immediate effect of the stimulation. Recording EEG signals during the stimulation will offer insights into the feasibility of conducting concurrent tTIS-EEG recordings, as well as source signal propagation.

EEG signal analysis will be done using MATLAB, and the preprocessing steps will include signal noise and artifact removal. Independent component analysis (ICA) will be used to remove electrooculogram (EOG) artifacts. EEG signals will be bandpass filtered at 0.5–40 Hz to remove movement and instrumentation noise. A simple power estimation will be conducted on the resting-state EEG signals. Time and frequency domain analysis will be conducted on segmented auditory MMN EEG signals. The segmentation will divide the EEG signals into short-term epochs of 500 ms (−100 to 400 ms). The analysis will then be conducted on these time segments. Time domain analysis will be used for the auditory MMN tasks to estimate the average difference between deviant and standard ERP responses in order to extract the amplitude and latency of N1 and P1 ERPs. Time domain signal processing techniques will be used to extract statistical metrics such as root mean square, signal variance, and variance of the first derivative of the ERP signals. Frequency domain analysis on the segmented EEG signals will extract energy ratios and power spectral density at each EEG frequency band. Subjective answers obtained as categorical variables will be used in labeling the EEG segments, and machine learning techniques will be implemented to classify the signal segments on the basis of response and remission as well as to determine the combined role of MRI metrics, clinical variables, and EEG signal features in assessing treatment response to tTIS.

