Our primary aim is to demonstrate target engagement of the sgACC with tTIS in participants with MDD using the resting-state fMRI, arterial spin labeling (ASL), and diffusion-weighted MRI, as evidenced by pre- vs. post-treatment changes in its intrinsic activity, functional connectivity (FC), perfusion, and anatomical connectivity with other brain regions. We hypothesize that in participants with MDD, a course of 10-day active 130 Hz tTIS will induce engagement of the sgACC post-treatment, which will be superior to sham. Target engagement will be measured as pre- vs. post-treatment change in: (a) resting-state blood-oxygen-level-dependant (BOLD) activity, quantified by power in the BOLD characteristic frequency range (0.015–0.08 Hz), (b) perfusion metrics of cerebral blood flow (CBF), and (c) BOLD activity and CBF in resting-state functional and anatomical networks, or brain regions that are strongly coherent with the sgACC functionally and connected anatomically. We hypothesize that we will observe (a) an increase in BOLD activity in sgACC voxels in tTIS arms but not the sham due to the direct stimulation of the area, (b) an increase in CBF in sgACC voxels in tTIS arm but not the sham due to the direction stimulation of the area, (c) an increase in FC between sgACC and dorsolateral prefrontal cortex (dlPFC), ventromedial prefrontal cortex (vmPFC), and insula – the nodes that display reduced baseline resting-state FC in unmedicated MDD patients compared to healthy controls (Murrough et al., 2016; Wang et al., 2018; Cheng et al., 2021), (d) a significant association between changes in the FC of the sgACC with the abovementioned nodes and anatomical connectivity. Our secondary aim is to demonstrate, using a randomized sham-controlled design, the feasibility, tolerability, and therapeutic potential of repetitive tTIS in participants with MDD. We hypothesize that a 10-day active 130 Hz tTIS will produce significantly greater improvement than sham stimulation in scores of standardized clinical measures of mood symptoms severity in MDD, anxiety, quality of life, and functional impairment. We will also perform exploratory analyses of (a) pre- vs. post-stimulation changes in whole-brain resting-state FC of the sgACC, (b) pre- vs. post-stimulation changes in resting-state electroencephalography (EEG) spectral power after a single session of tTIS and over the course of 10 sessions, (c) pre- vs. post-stimulation changes in the amplitude and latency of the auditory mismatch negativity (MMN) event-related potentials (N1 and P1) after a single session of tTIS and over the course of 10 sessions, (d) feasibility of performing concurrent EEG acquisition during tTIS (termed tTIS-EEG), and (e) source signal propagation during concurrent tTIS-EEG using our proposed configuration for the stimulation of the sgACC with tTIS.

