### 3.11 Electroencephalography

Before, during, and after tTIS session at Visits 1, 5, and 10, participants will undergo a 42-min EEG data collection, which includes: (1) pre-stimulation EEG at rest with eyes open (3 min); (2) pre-treatment EEG during the auditory MMN task (Näätänen et al., 1978) (3 min); (3) concurrent EEG acquisition during tTIS (30 min); (4) post-stimulation EEG at rest with eyes open (3 min); and (5) post-stimulation EEG during the auditory MMN task (3 min). A 32-channel BioSemi ActiveTwo EEG acquisition system (Cortech Solutions Inc., Wilmington, NC, United States) will be used to collect surface EEG measurements. The desired sampling frequency is 4,096 Hz. Each sample will be quantified at 16 bits, and the digital data will be stored in a secured server for further signal analysis of time and spectral domain features. Auditory MMN is an event-related potential that appears in neurophysiological recordings during a sequence of repetitive sounds that is interrupted by an occasional “oddball” sound, which differs from other sounds in duration or frequency (Garrido et al., 2009). The MMN reflects the flow of the current through NMDA receptor-mediated ion channels and could be used as a biomarker to test whether new interventions influence NMDA receptor responsiveness in study participants (Näätänen, 2001; Garrido et al., 2009; Zhou et al., 2013).

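### The protocol does not settle which component is the MMN-task outcome: the rationale is the MMN, but the measures named are N1 and P1, taken from the deviant-minus-standard difference

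*Protocol article*

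**What the plan says.** Three places in the protocol article bear on the outcome of the auditory task.

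- **Section 3.11 (Electroencephalography)** describes a single potential: "Auditory MMN is an event-related potential that appears in neurophysiological recordings during a sequence of repetitive sounds", evoked when an occasional odd sound breaks the sequence. It gives the reason for measuring it, namely that it "could be used as a biomarker to test whether new interventions influence NMDA receptor responsiveness in study participants". N1 and P1 are not mentioned there. The task is run before and after stimulation at Visits 1, 5 and 10.
- **Section 2 (Objectives and hypotheses)**, exploratory analysis (c), sets the outcome as "pre- vs. post-stimulation changes in the amplitude and latency of the auditory mismatch negativity (MMN) event-related potentials (N1 and P1"), so the parenthesis equates the MMN potentials with N1 and P1.
- **Section 3.12.3 (Secondary outcomes: electroencephalography)** gives the extraction rule. The time-domain analysis is used "to estimate the average difference between deviant and standard ERP responses in order to extract the amplitude and latency of N1 and P1 ERPs". The same section plans to "extract statistical metrics such as root mean square, signal variance, and variance of the first derivative of the ERP signals", adds spectral features, and uses EEG features in a machine-learning classification of response and remission. It says of the EEG work: "These analyses will be exploratory".

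**The concern.** The quantity that justifies the task and the quantities named for extraction are different things. The deviant-minus-standard difference is the waveform that isolates the response to deviance, which is the MMN as Section 3.11 describes it. It is a poor place to measure N1 and P1, because whatever part of them is the same for both tones is subtracted out. The plan therefore builds the waveform suited to the MMN and then names two other components as what is to be read from it.

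Two analysts could follow this text and report different quantities: one the negative deflection of the difference wave, the other N1 and P1 peaks sought in that wave or in the tone averages. If N1 and P1 in the difference wave showed no change, a reader could take this as no effect on the NMDA-related response, although neither the MMN's amplitude nor its latency had been declared as the measure. The same uncertainty passes into the EEG features used for classification.

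**Working it through.** The protocol gives no figure to reproduce here; the only nearby number, the epoch, is consistent with itself (400 − (−100) = 500 ms). The check is a comparison of the three sections, followed by the algebra of the subtraction.

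**Step 1. Sections side by side**

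| Place | Component named | Waveform named |
|---|---|---|
| Section 3.11 | MMN | none |
| Section 2, exploratory (c) | MMN, labelled N1 and P1 | none |
| Section 3.12.3 | N1 and P1 | deviant-minus-standard difference |

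The MMN's amplitude and latency are named only in Section 2, and there under the labels N1 and P1. The rule that says what is extracted, and from which waveform, names N1 and P1 alone. The root mean square and variance metrics apply to the ERP signals in general and are not tied to an MMN peak or window.

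**Step 2. What the subtraction keeps**

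At a given latency, write the averaged response to the standard as S = C and to the deviant as D = C + M. C is the activity common to both tones and M is the deviance-related part. Then

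D − S = (C + M) − C = M.

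If stimulation shifts the common part by δ and the deviance-related part by μ, the change in the difference is

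[(C + δ) + (M + μ) − (C + δ)] − M = μ.

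The shift δ, which is where an equal effect on N1 or P1 would appear, drops out. If the shift in N1 differs between tones (δ_D for the deviant, δ_S for the standard), the change in the difference is (δ_D − δ_S) + μ. The part of N1 that survives is then mixed with any MMN change at the same latency.

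**Step 3. Illustration**

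The protocol gives no amplitudes, so all values here are assumed. Let N1 be −5 µV to both tones before stimulation, let the standard go to −7 µV afterwards (a change of −2), let μ = 0, and vary the deviant.

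| Deviant after | Difference before | Difference after | Change in difference | Change in standard average |
|---|---|---|---|---|
| −5 | −5 − (−5) = 0 | −5 − (−7) = +2 | +2 | −2 |
| −7 | 0 | −7 − (−7) = 0 | 0 | −2 |
| −8 | 0 | −8 − (−7) = −1 | −1 | −2 |
| −9 | 0 | −9 − (−7) = −2 | −2 | −2 |

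The zero in the second row follows from assuming equal effects. The table shows only that the change read from the difference depends on how unequal the tone effects are, not on the size of the N1 effect itself.

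**Step 4. Reach**

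The rule applies to every task recording: 2 per visit × 3 visits × 30 participants = 180 at most, before any dropout. This counts the recordings affected; it does not measure bias.

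**The case against.** The strongest reply is that this is a matter of labels. The plan does form the deviant-minus-standard difference, and Section 2 does name MMN amplitude and latency as the outcome. Read together, Sections 2 and 3.12.3 may mean that the deflections of the difference wave are measured and called N1 and P1. Other waveform and spectral metrics are planned in a list that is open-ended. Section 3.11 presents the MMN only as a possible biomarker. Windows and peak rules belong in a full protocol or analysis plan, and the EEG work is declared exploratory.

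Most of this stands, and it rules out three stronger readings that a reader might infer.

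- **That the MMN is never measured.** The documents do not support this. The difference wave is estimated, and the text cannot show whether the MMN is omitted or measured under other labels.
- **That N1 and P1 from the difference are largely noise.** This would need the responses to both tones to be equal. The protocol does not say so, and Section 3.11 says the odd sound differs in duration or frequency, so some tone-specific activity may survive.
- **That a null result would say nothing about the NMDA-related response.** The contrast between tones is still estimated, and other metrics of the ERP signals are listed.

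What the reply does not remove is the extraction rule itself. The article states which components are taken and from which waveform. This is not a detail left to another document: a fuller plan that named the MMN would have to correct the rule, not merely add to it.

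**Conclusion.** The point holds as an inconsistency to reconcile. Section 3.11 rests the task on the MMN, while Sections 2 and 3.12.3 name N1 and P1 as the amplitude and latency measures, and Section 3.12.3 takes them from a waveform in which activity common to both tones cancels. Followed literally, a stimulation effect on N1 or P1 that is equal for both tones would be missed, and the MMN's own amplitude and latency are not identified as extracted measures. The cancellation is exact for whatever part is common. How large that part is cannot be told from the documents, so no bias is quantified.

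The consequence is small. It reaches an exploratory EEG outcome (placed under a secondary-outcomes heading but declared exploratory in the text) and the EEG features used in the classification analysis. The imaging primary outcome, the clinical analysis and the sample size do not depend on it.

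**What to change.** In Section 2, exploratory analysis (c), and in Section 3.12.3, name MMN amplitude and latency as the measures taken from the deviant-minus-standard difference wave. If N1 and P1 are also of interest, list them separately and take them from the tone-specific averages, for example the average response to the standards. Section 3.11 can then stand as it is. State which of these measures enter the classification analysis.

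The cost is a few words of analysis text. The recordings, task and epochs stay the same, and no data are lost. If the change is made before the EEG data are analysed, it cannot be influenced by the results.

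### Band power and energy ratios taken from 500-ms MMN epochs have only 2 Hz resolution, so the lowest EEG bands cannot be separated; minor, limited to exploratory spectral features

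*Protocol article*

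**What the plan says.** All of the relevant rules are in section 3.12.3 of the protocol article.

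- Filter: "EEG signals will be bandpass filtered at 0.5–40 Hz to remove movement and instrumentation noise".
- Which recordings are segmented: "Time and frequency domain analysis will be conducted on segmented auditory MMN EEG signals".
- Epoch length: "The segmentation will divide the EEG signals into short-term epochs of 500 ms", running from 100 ms before to 400 ms after the stimulus.
- What the later steps use: "The analysis will then be conducted on these time segments".
- Spectral output: "Frequency domain analysis on the segmented EEG signals will extract energy ratios and power spectral density at each EEG frequency band".

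Resting-state EEG is handled separately: "A simple power estimation will be conducted on the resting-state EEG signals". The article does not tie that estimate to the 500-ms epochs.

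The same section calls the EEG analyses exploratory. It also sends EEG features, with MRI and clinical variables, into a machine-learning step on response and remission. Section 3.11 gives a sampling rate of 4,096 Hz and 3 minutes for each MMN recording.

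**The concern.** The epoch length suits an ERP average but is short for a spectrum. The filter keeps activity down to 0.5 Hz, and the spectral step promises a value for every band, yet half a second of signal holds only a fraction of a cycle at the lower end of that range. The article names no longer window for the spectral step and leaves out no low band. Followed as written, the rule would report delta and theta values, and ratios built on them, that the epochs cannot support.

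What is at stake is the reading of the MMN spectral features and of the classifier inputs derived from them. A change in one low band could be labelled as a change in its neighbour, in a pilot whose data are meant to inform a larger trial.

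**Working it through.** **Inputs from the article.** Epoch from −100 to 400 ms, pass band 0.5–40 Hz, sampling at 4,096 Hz, MMN recording of 3 min.

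**Epoch length.** 400 − (−100) = 500 ms, as stated, so T = 0.5 s.

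**Resolution (no assumption needed).** 1/T = 1/0.5 = 2 Hz. By the sampling rate: N = 4,096 × 0.5 = 2,048 samples, and 4,096/2,048 = 2 Hz. Faster sampling does not change this, and zero-padding only interpolates between the same values.

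- Cycles per epoch: 0.5 Hz × 0.5 s = 0.25; 1 Hz × 0.5 s = 0.5.
- Main lobe, null to null: 2/T = 4 Hz without a taper, 4/T = 8 Hz with a Hann taper.

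**Bins per band (assumed edges: delta 0.5–4 Hz, theta 4–8 Hz).** Delta has one bin of its own (2 Hz). Theta has two (4 and 6 Hz), and the 4 Hz bin lies on the boundary. The main lobe is at least as wide as either band.

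**Single tones.** A 3 Hz tone lies midway between the 2 and 4 Hz bins. Without a taper each receives about [sin(0.5π)/(0.5π)]² = 0.637² = 0.41 of its power. Adding the 6 Hz bin and the negative-frequency term, 46% of this delta tone falls in theta (50% with Hann). A 1 Hz tone puts 41–48% of its power in the 0 Hz bin, so some low-frequency power is lost to every band and does not move to theta.

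**Broadband signal (assumed spectra 1/f, 1/f^1.5 and 1/f^2; Hann or no taper; no baseline removal, mean removal or prestimulus baseline).** Power recovered from 500-ms epochs, relative to the true value:

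| 4 Hz bin counted as | Delta | Theta |
|---|---|---|
| theta | 25–87% | 129–220% |
| delta | 35–113% | 77–108% |

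Delta was understated in 35 of the 36 settings (3 slopes × 2 tapers × 3 baseline rules × 2 placements of the 4 Hz bin).

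**Shares and ratios (assumed 1/f background plus a 10 Hz peak; 4 Hz bin in theta).** These runs used no taper with mean or prestimulus baseline removal, or a Hann taper.

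- A true delta share of 35% reads as 16–21%, and a true theta share of 12% as 18–19%.
- The alpha share moves from 33% to 39–42%, because the low-band loss changes the total.
- The delta/alpha ratio falls from 0.353/0.332 = 1.06 to between 0.158/0.421 = 0.38 and 0.207/0.386 = 0.54.

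**Dependence on unstated choices (a similar spectrum, true delta share 37%).**

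- 4 Hz bin in theta: delta reads 17–22%, or 32% with a prestimulus baseline followed by Hann. A pure 50% rise in delta raises theta by about 21% (19–20% under the preceding spectrum).
- 4 Hz bin in delta: delta reads 28–41%, and the spurious theta change is 0–4%. How fully it vanishes depends on spectral slope and taper.

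**Longer segments (no or mean removal).** Delta power is recovered at 0.92–1.01 of its true value with 2-s segments (0.5 Hz spacing) and 0.95–0.99 with 4-s segments (0.25 Hz). With 500 ms the range is 0.25–0.77. Under the 10 Hz-peak spectrum, 4-s windows cut the spurious theta rise to about 3%.

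**The case against.** The strongest reply is that this matters little and that its direction is not fixed. The article calls the EEG analyses exploratory. Among the exploratory analyses in section 2, the spectral one concerns resting-state EEG, and the MMN one concerns ERP amplitude and latency. Both are untouched. Section 3.8 says more broadly that resting-state and task EEG serve to assess oscillations, but no hypothesis test or sample-size claim rests on MMN band power. The epoch length is common to both arms and all visits, and a classifier can use a feature whose band label is imprecise. All of this stands and keeps the severity low.

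A second reply is that band edges, taper and estimator belong in a fuller document. That stands for those details, and it is why no single percentage can be asserted. It does not answer the resolution point, because the article itself states the epoch length and says that spectra for each band come from those epochs.

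A third reply is that long continuous windows measure something else: they mix standard and deviant stimuli and give background power instead of stimulus-locked power. The simulations contain ongoing activity only and no evoked response, so they do not test event-related spectral features. This is correct, and it shapes the fix.

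A reader might infer that delta is always understated and always spills into theta, or that baseline correction strips out the slowest activity. The documents support neither: they give no band edges and state no baseline correction, and the theta excess largely disappears when the 4 Hz bin is counted as delta.

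**Conclusion.** The point holds as a minor one. From the article's own figures, 500-ms epochs resolve 2 Hz and cannot separate the lowest bands of a 0.5–40 Hz signal. Delta and theta power from these epochs, and any ratio that includes them (including shares of total power), are unreliable. That much needs only the conventional placement of those bands.

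Size and direction rest on assumed band edges, a 1/f-type spectrum, the taper and the baseline handling. Under those assumptions delta is usually too low. A true 50% delta rise shows as roughly a 20% theta rise if the 4 Hz bin is theta, and as a small change if it is delta.

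The scope is the exploratory MMN spectral features and the classifier inputs built on them. It would go too far to infer that the pilot will carry the wrong oscillatory marker forward or that the comparison between arms is biased. The resting-state spectral analysis is separate, ERP amplitude and latency and the MRI outcomes do not use these spectra, and the shared epoch length mainly blurs and mislabels low-band effects.

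**What to change.** In section 3.12.3, keep the 500-ms epochs for ERP amplitude and latency. From those epochs, report band power and energy ratios only for bands from about 8 Hz upward, and keep the lower bands out of the denominators as well.

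If delta and theta power during the MMN task are wanted, compute them from segments of at least 2 s, for example 2–4 s, of the continuous 3-min record. Label the result as ongoing task-period power, not stimulus-locked power. State the band edges, including which band the 4 Hz bin belongs to, with the taper and any baseline step.

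The cost is a sentence or two and a change in the analysis script, with no new data. The downsides are that low-band event-related power is not reported and that there are fewer segments per recording: 180/2 = 90 of 2 s, or 180/4 = 45 of 4 s.

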### 3.4 Sample size considerations

Based on studies in TES with fMRI, block design, and use of computational iterative neurostimulation (Ghobadi-Azbari et al., 2021), we expect that 30 participants will have adequate power to demonstrate target engagement of the sgACC. The proposed sample size (*n* = 30) is also based on the overall goal of (a) reasonably assessing the feasibility outcomes and (b) estimating the variability of the clinical outcome measures and is consistent with published recommendations for pilot trials designed to estimate standard deviations for larger future randomized controlled trials when the effect size is small-to-medium (Lancaster et al., 2004; Whitehead et al., 2016). As such, based on sample sizes used in pivotal TES studies (Berlim et al., 2013), we expect that 30 participants will be adequate to demonstrate the feasibility, tolerability, safety, and therapeutic effect of tTIS. Moreover, the pilot study will provide effect size estimates to design a definitive efficacy trial.

For this pilot study, to have a 90% power (i.e., being 90% confident that the effect is true and that it is not a type I/II error), the top end of the two-sided 95% confidence intervals will be the maximum confidence of having a true difference between active tTIS and sham arms. If there is no difference between active tTIS and sham arms, then *p* ≥ 0.051 will indicate no difference with a 90% confidence, and if there is a difference, then *p* ≤ 0.05 will indicate the difference with a 90% confidence. To have the medium effect size of *f* = 0.25 for the mixed-model analysis of variance (Cohen, 2013), 30 patients (15 per group) are required to have a 90% power. We anticipate having a 15% dropout rate in the randomized phase of the study due to side effects or lack of adherence to protocol and approximately a 50% response rate in the acute phase of treatment. A sample size of 15 per group will give us precise estimates of variability in the clinical outcome, namely a change in the Hamilton Depression Rating Scale 17-Item (HAM-D-17) (Hamilton, 1960) score over time (Korn et al., 2012; Cohen, 2013), and this sample size is within the recommended total sample sizes for a precise estimate of the standard deviation and correlation for HAM-D-17 scores to use in the future sample size calculation for a definitive larger scale trial (between *n* = 24 and 50) (Julious, 2005; Sim and Lewis, 2012; Billingham et al., 2013).

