Regions strongly anatomically connected to sgACC will be identified using diffusion-weighted MRI tractography. For these analyses, raw diffusion-weighted MRI scans will be preprocessed, denoised, and reconstructed using QSIPrep (Cieslak et al., 2021). The preprocessing and denoising steps include conforming image and gradient orientation, head-motion correction, distortion correction, registration, and normalization. White matter tracts can be extracted from the fiber tractography during reconstruction. The cortical terminations of the sgACC-seeded streamlines will define brain regions anatomically connected to the sgACC. We will conduct additional pre- vs. post-stimulation comparisons on those regions specifically in terms of their signal variance and FC patterns, as described above, and with specific interest in the anatomical connectivity between the sgACC and bilateral dlPFC, vmPFC, and insula.

In addition, we will investigate whether these target engagement metrics are associated with clinical outcomes, as quantified by linear regression analyses. Finally, we will compute tTIS electric field models of T1-weighted MRI images to determine *post hoc* the specific pattern of tissue stimulation experienced by each participant. We will test whether these e-field-computed electrical current intensities are correlated with the regional target engagement metrics outlined above using linear regression models.

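### The EEG features are tied to clinical outcome only through response and remission labels cut from the depression scores, which discards about a third to a half of the outcome information in roughly 26 completers.

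*Protocol article*

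**What the plan says.** Section 3.12.2 of the protocol article sets the two labels. For response, "response will be defined as a ≥50% reduction in HAM-D-17 and QIDS-SR-16 total scores at Visit 10". For remission, "Remission will be defined as a HAM-D-17 total score of <8 at Visit 10". Both are cuts of totals that Table 2 schedules at baseline and Visit 10, so the uncut scores will be available.

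Section 3.12.3 then uses the labels for the EEG data: "machine learning techniques will be implemented to classify the signal segments on the basis of response and remission". The same sentence extends the work to the joint contribution of MRI, clinical and EEG features to assessing treatment response. The section calls the EEG analyses exploratory and states no power for them.

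Two other analyses use the uncut scores, but neither covers this ground. In 3.12.1, for the MRI metrics only, "we will investigate whether these target engagement metrics are associated with clinical outcomes, as quantified by linear regression analyses". In 3.12.2 a mixed-effects model compares the arms over time on continuous measures.

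**The concern.** In the arm comparison the cut does little harm, because the mixed model analyses the full scale alongside it. For EEG prediction there is no such counterpart: the cut label is the only stated clinical target. The article gives no reason for treating EEG differently from the MRI metrics, which go into a linear regression.

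The cut removes information that the trial has already paid for. Participants who improve by 48% and by 0% receive the same label, while 48% and 52% receive opposite ones. With about 26 outcomes, there is little information to spare.

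The abstract says the data will be used to optimise tTIS and design a large efficacy trial. A weaker search for features that go with improvement feeds directly into that use. The point concerns the label, so it remains whether classification is done per signal segment or per participant.

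**Working it through.** **The plan's own power figure.** Section 3.4 states that "30 patients (15 per group) are required to have a 90% power", for an effect size f of "0.25 for the mixed-model analysis of variance". This belongs to the arm-by-time comparison, not to the EEG work. It can be reproduced with a noncentral F for the group-by-time interaction, λ = f²·N·m/(1 − ρ), if one assumes m = 4 measurements and ρ = 0.5 (neither is stated). Then λ = 0.0625 × 30 × 4 / 0.5 = 15, with 3 and 84 degrees of freedom, and power is 90.3%. It says nothing about the prediction analysis, for which no figure exists to reproduce.

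**Inputs for the present point.**
- Completers: section 3.4 says "We anticipate having a 15% dropout rate in the randomized phase of the study" and gives the rate as 15%. 30 × 0.85 = 25.5, taken as 26.
- Response share: about 50% (section 3.4).
- Remission share: 16% to 22%, the pooled range quoted for TES and TMS in section 1.1. Expected remitters: 26 × 0.16 = 4.2 to 26 × 0.22 = 5.7.
- Test level: two-sided 5%, in line with "the top end of the two-sided 95% confidence intervals" in section 3.4.
- Correlation r between a feature and the change score: not in the document. A range of 0.2 to 0.7 is shown.

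**Information kept by the cut.** For a normal outcome cut so that a share p is labelled positive, the correlation is multiplied by φ(c)/√(p(1 − p)), where c is the cut-point. The information kept is the square, φ(c)²/(p(1 − p)), and does not involve r.

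| Share p | φ(c) | Information kept | 26 act like |
|---|---|---|---|
| 50% | 0.399 | 0.637 | 16.6 |
| 22% | 0.296 | 0.511 | 13.3 |
| 16% | 0.243 | 0.440 | 11.5 |

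**Illustrative power.** Feature and change were simulated as bivariate normal with n = 26. The correlation test on the continuous change was compared with the same test after cutting the change score at its upper p. Type I error was about 5% in both. Points lost are in brackets.

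| r | Continuous | 50% cut | 22% cut | 16% cut |
|---|---|---|---|---|
| 0.2 | 16% | 12% (4) | 11% (5) | 9% (7) |
| 0.3 | 32% | 22% (10) | 18% (14) | 16% (16) |
| 0.4 | 54% | 36% (18) | 30% (24) | 25% (29) |
| 0.5 | 77% | 55% (22) | 44% (33) | 38% (39) |
| 0.6 | 92% | 75% (17) | 61% (31) | 53% (39) |
| 0.7 | 99% | 90% (9) | 78% (21) | 69% (30) |

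If only the 13 active-arm completers are used, r = 0.5 gives 44% with the continuous score, 28% with the 50% cut and 18% with the 16% cut.

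**The case against.** **The power figures rest on an assumed correlation and a one-feature test.** This stands. The plan is a multi-feature classifier with no stated hypothesis test, and no calculation here shows by how much a penalised regression would outperform it. The table shows the cost of the label and is not the power of the planned analysis. A reader might infer that the trial is known to lose up to 40 points of power; the document does not support that.

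**The remission figures cut the change score, whereas the plan cuts the final score.** This also stands. A feature's correlation with the final score depends on baseline and change spreads that the document does not give. A check with assumed spreads gave a similar or larger loss, but other spreads could make it smaller.

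**Remission may not be rare.** Section 1.1 also cites 54% remission in a tACS study, and the article describes tTIS as a form of tACS. A 54% share keeps about the same information as a 50% share, so the larger losses would not arise. The 10 to 22 points for the response label remain.

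**A real predictor need not be missed.** At r = 0.5 and 0.6 the response label still gives 55% and 75%. At r = 0.3 the continuous score gives only 32%. The small sample is the main limit, so it would be wrong to infer that the cut makes missing a real predictor likely.

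**The combined analysis is not expressly yes/no.** The sentence says treatment response, and the article elsewhere uses that phrase in a general sense. The definition of response in 3.12.2 makes the binary reading natural but not certain.

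**Remission depends on baseline severity, but so does raw change.** That argument does not single out the cut; it is a reason to put the baseline score in the model.

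**The work is exploratory, and details may sit in a document not shown.** Exploratory status keeps the matter minor. Model details may indeed be elsewhere, but the outcome label is a choice the article states.

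**Conclusion.** The point holds as a minor one. The article fixes cut labels as the only stated clinical target for the EEG features, while it relates the MRI metrics to clinical outcomes by linear regression.

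The firmest measure of the cost is the information kept: about 64% at a 50% response rate and about 44% to 51% at a remission share of 16% to 22%. It assumes a normally distributed outcome and those shares. The power losses of about 10 to 22 points (response label) and up to about 40 points (rare remission label) also require r between 0.3 and 0.6 and a single participant-level feature; at r = 0.2 they shrink to 4 to 7.

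Nothing here touches the arm comparison, the 90% power statement or any confirmatory conclusion. What is weakened is the use of these exploratory results to optimise tTIS and plan the larger trial.

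**What to change.** In section 3.12.3, make the participant's continuous change in HAM-D-17 total from baseline to Visit 10 the main prediction target, with QIDS-SR-16 change as support. Fit it at participant level by penalised regression, with baseline score and arm in the model. State that the combined EEG, MRI and clinical analysis uses the same target. Keep classification by response and remission as a descriptive supplement.

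The cost is analysis wording: no new data, visits or participants. The small downside is that performance is then reported as prediction error or explained variance, which clinicians know less well than classification accuracy; the supplement still supplies the latter.
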